### Data monitoring

Data monitoring and management will be performed by Stemexcel Technology Company (Beijing Stemexcel Technology Co., Ltd., Beijing, China).

The trial data are recorded in the electronic data management system (DAS for EDC). The CRF is designed according to the protocol in order to collect trial data and to define trial procedures. The form is finalized after sponsors’ approval. CRF data from each participant will be examined and verified by two investigators at a given study site. The entered data will be systematically checked by medically trained personnel. Errors will be corrected by medically trained personnel and communicated to the site investigators. The CRF will be inspected by an assigned person at regular intervals throughout the trial in order to verify the protocol compliance. The entered data should be complete, consistent and accurate.

### SAEs

Severe adverse drug reaction/events (SAEs) refer to the following conditions: death, life-threatening or permanent or significant disability, permanent functional injury to the organs, hospitalization for emergencies or prolonged hospitalization.

Once a SAE is confirmed in a patient, this patient will be removed from the trial and a report should be filled within 24 hours. A full report regarding SAEs should be filled to the sponsor and SFDA. The ethics committee of pharmaceutical affairs of ONET will conduct an investigation to identify causes of SAEs and decide whether the trial will be terminated. The severity of SAE, its relationship with the trial medication, and treatments should be recorded in the CRF. The above conditions are delivered to the ethics committee of all participating hospitals.

### Interim analysis

Interim analysis will not be conducted.

### Auditing

Before the trial is ended, a serial quality control audit of the database will be conducted.

### Methodology

The ATOCH study is designed based on our previous experience in treating CSDH with atorvastatin, showing that 22 out of 23 patients achieved complete hematoma elimination during the follow-up period after atorvastatin treatment. We, therefore, expect a significant volume reduction in the hematomas of patients on atorvastatin. However, since this is a conservative treatment trial of a clinical condition that is traditionally treated surgically, we limit our recruitment to patients who have a small-medium volume of CSDH and whose MGS-GCS is less than 3. To reduce adverse risks, especially patients on placebo, all patients will be closely monitored for acute neurological deterioration. If neurological symptoms deteriorate during the trial, patients will receive an emergency head CT scanning and necessary surgery. Such patients will be removed from the trial.

Except for rhabdomyolysis and impact on liver function, atorvastatin is considered to be generally very safe. Thus, we do not plan to waive SAE for this trial protocol. If a patient develops any suspected related side effects, he or she will be immediately excluded. If atorvastatin-related side effects are confirmed, treatment will be terminated and affected patients will be followed for 6 months.

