### Exclusion criteria

The exclusion criteria are: (1) allergic to statins or their ingredients; (2) cerebral herniation; (3) subdural hematoma caused by tumors, hematologic diseases or other known severe comorbidities such as multiple organ failure, uncontrolled diabetes mellitus and heart failure; (4) abnormal liver function or liver diseases including uncontrolled hepatitis; (5) other diseases that may interfere with the study as determined by 2 attending neurosurgeons; (6) patients on oral statin medication for more than 1 week before randomization or who are expected to take statins in the next 6 months; (7) patients on oral steroids for more than 1 week before randomization or who are expected to take such medications in the next 6 months; (8) a participant in clinical trials in the past 4 weeks; (9) pregnancy or breastfeeding; (10) failure to complete the trial by poor compliance; (11) other conditions that render a patient unsuitable for the trial as determined by the study investigators.

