### Treatment and intervention

*Atorvastatin:* oral intake of a 20 mg Atorvastatin tablet daily for 8 weeks.

*Placebo:* oral intake of a placebo tablet daily for 8 weeks.

At the end of the 8-week treatment, the volume of hematoma will be evaluated by CT scan for the following outcomes:A hematoma disappears or is significantly reduced from the size measured before the treatment. Regardless of whether a smaller hematoma remains, the patient will enter into the follow-up period and should not be continuously treated with atorvastatin.A hematoma does not change significantly or increases by CT scan at the end of 8 weeks of treatment (this can occur in patients who receive placebo). At the end of atorvastatin treatment, attending surgeons can decide if these patients need to receive surgery. The detailed medication and treatment during the process will be continuously recorded for 24 weeks.For any patients whose hematoma increases as determined by CT scan and/or neurological deficits progress during the follow-up period, he or she may undergo surgery. The detailed medication and treatments during the process will be recorded for 24 weeks.

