### Concomitant care

All patients in the study will receive routine laboratory assessments, including complete blood count (CBC), coagulation (international normalized ratio, INR), liver and renal function, blood lipids and urinalysis. Head CT images will be recorded in Digital Imaging and Communication in Medicine (DICOM) format and evaluated centrally in a triple-blinded manner. Blood samples will be analyzed in a local laboratory and saved in a Case Report Form (CRF) format. The 4 regular follow-up visits are scheduled at the 4^th^, 8^th^, 12^th^ and 24^th^ weeks after the initiation of atorvastatin treatment.

The ACEIs (such as perindopril, captopril, enalapril) are reported to eliminate CSDH [9, 28] and are thus their use is not allowed during the course of atorvastatin treatment. Anticoagulants (warfarin or new oral anticoagulants), antiplatelet drugs (aspirin, clopidogrel) or *Xuesaitong* (traditional Chinese medicine for activating blood circulation) can potentially interfere with hematoma absorption and are not recommended during the treatment. However, these patients will not be exclusively excluded from the trial participation. The following drugs may potentially interact with statins and/or cause adverse events [29] and will not be recommended during the treatment: red yeast rice, erythromycin, fibrates, cyclosporin, macrolide antibacterials, azole antifungals, tacrolimus, gemfibrozil, troglitazone, and itraconazole. The use of any medications will be recorded if they are used concomitantly during atorvastatin treatment in CRF, including name, dosing and duration of these medications.

Most participants are treated as outpatients receiving conventional and standard cares such as rest and pain relief. Family members are responsible for monitoring patients for progress in neurological symptoms such as worsening headache. If a patient is reported to have worsening symptoms, he or she will be further evaluated by two attending physicians for neurological deficits. These patients may be admitted during the trial for treatment of progressing neurological deficits and discharged when their symptoms are relieved significantly. Whether these patients remain on the trial as inpatients will be determined on a case-by-case basis by two participating investigators/surgeons.

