### Outcomes

The primary outcome is the change of hematoma volume 8 weeks after atorvastatin treatment on non-enhanced CT scan.

Secondary outcomes are changes of hematoma volume at the 4^th^, 12^th^, and 24^th^ weeks; MGS- GCS, GOS and ADL-BI scores; and improvements in neurological symptoms and signs and laboratory tests.

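### Three removal rules take randomised patients out of the trial for post-randomisation events, so week-8 volumes can go missing for outcome-related reasons, and other sections contradict them

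*Protocol article*

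**What the plan says.** Three rules in the protocol article end a randomised patient's participation because of something that happens after randomisation:

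- **Deterioration with surgery** (Methodology): "patients will receive an emergency head CT scanning and necessary surgery. Such patients will be removed from the trial".
- **Any confirmed SAE** (SAEs): "Once a SAE is confirmed in a patient, this patient will be removed from the trial". The definition includes emergency hospitalisation, and the rule makes no exception for unrelated events.
- **Any suspected related side effect** (Methodology): "If a patient develops any suspected related side effects, he or she will be immediately excluded".

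Other places treat some of the same patients differently:

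- Concomitant care, on patients admitted with progressing deficits: "Whether these patients remain on the trial as inpatients will be determined on a case-by-case basis by two participating investigators/surgeons".
- Timeline schedule, Table 2: surgery conversion has an entry at every visit from day 1 to week 24.
- Treatment and intervention, on surgery during follow-up: "The detailed medication and treatments during the process will be recorded for 24 weeks". The same recording applies to patients considered for surgery at the end of week 8.
- Methodology, on confirmed side effects: "treatment will be terminated and affected patients will be followed for 6 months".

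The endpoint at stake is in Outcomes: "The primary outcome is the change of hematoma volume 8 weeks after atorvastatin treatment on non-enhanced CT scan".

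Exclusion criteria, item 10, also lists "failure to complete the trial by poor compliance".

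**The concern.** The drug is meant to shrink the hematoma without surgery, so deterioration leading to surgery is close to being the treatment failure itself. A patient removed for it before week 8 has no week-8 CT because of how the treatment turned out. Removal for an SAE or a suspected side effect may depend on the assigned drug. The patients left at week 8 are then a selected group in each arm, and the protection of randomisation is weakened.

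The effect can run either way. If the drug works and failures are removed at the same rate in both arms, more placebo patients go and the difference shrinks. If removal rates differ between arms, a difference can appear where none exists. Safety follow-up after the triggering event may also stop early.

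An analysis plan cannot repair this afterwards. It can define an analysis set, but it cannot recover scans and assessments that sites had no instruction to obtain. Because the sections disagree, 16 centres may also handle the same kind of patient in different ways.

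**Working it through.** **Inputs from the document.** Assumed success 80% (drug) and 50% (placebo), 52 per arm at 80% power, 20% drop-out giving 126, and 200 planned, so 100 per arm (Sample size); two-sided test at 0.05 (Data analysis).

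**Inputs assumed.** The share f of non-responders removed before week 8. The document gives no value, so a range is shown.

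**The plan's own figure.** The pooled two-proportion formula for 80% versus 50% gives 39 per arm at 80% power (45 with continuity correction). The stated 52 is not reproduced at 80% power; it is the result at 90%. The total of 126 is 52 × 1.2 = 62.4, rounded up to 63, times 2. This does not affect the present point, because the planned 200 exceeds all these figures.

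**Scenario A: true 80% versus 50%, same f in both arms.** Of 100 randomised per arm, 100 − 20f remain on drug and 100 − 50f on placebo. If retained patients only are compared, the rates are 80/(100 − 20f) and 50/(100 − 50f). Power is Φ[(d − 1.96·SE0)/SE1], where d is the observed difference, SE0 the pooled and SE1 the unpooled standard error.

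For f = 0.5: 80/90 = 88.9% and 50/75 = 66.7%, so d = 0.222. The pooled rate is 130/165 = 0.788, SE0 = 0.0639 and SE1 = 0.0637. (0.2222 − 1.96 × 0.0639)/0.0637 = 1.52, and power is 93.6%.

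| f | Retained (drug/placebo) | Observed rates | Difference | Power |
|---|---|---|---|---|
| 0 | 100/100 | 80.0% vs 50.0% | 30.0 points | 99.6% |
| 0.3 | 94/85 | 85.1% vs 58.8% | 26.3 points | 97.9% |
| 0.5 | 90/75 | 88.9% vs 66.7% | 22.2 points | 93.6% |
| 0.8 | 84/60 | 95.2% vs 83.3% | 11.9 points | 65.2% |

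**Scenario B: no true effect, 50% in both arms, unequal removal.** With f = 0.4 in one arm and 0.2 in the other, 80 and 90 patients remain and the rates are 50/80 = 62.5% and 50/90 = 55.6%. The false difference is 6.9 points. With pooled rate 100/170 = 0.588, SE0 = 0.0756 and SE1 = 0.0753, the two-sided rejection probability is about 0.15 instead of 0.05. Swapping the arms reverses the sign. With equal f there is no bias here and the error stays at 0.05.

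**The sections side by side.**

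| Patient | Leaves the trial | Kept or followed |
|---|---|---|
| Worsening, admitted | SAEs, if the admission counts as an SAE | Concomitant care: case by case |
| Deteriorates, operated on before week 8 | Methodology | Table 2 has a surgery-conversion entry at each visit; Treatment and intervention is silent |
| Deteriorates, operated on in follow-up | Methodology, which covers the whole trial | Treatment and intervention: treatment recorded to week 24 |
| Side effect | Methodology, on suspicion | Methodology, 6 months once confirmed |

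Only removal before week 8 touches the primary outcome. Later removal affects the week-12 and week-24 assessments.

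**The case against.** Four objections have weight.

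1. A reader might infer that the primary comparison drops treatment failures and is therefore biased. The document does not say so. It names no analysis set for the primary outcome, leaving the trial is not the same as leaving the analysis, and the handling of missing values may be in an analysis plan that is not shown. This stands: the text supports exposure to bias, not bias as a fact. It does not answer the loss of data at source.

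2. A reader might count poor compliance as a fourth removal rule. It sits in the eligibility list, and nothing else in the article removes a randomised patient for it. It is a misworded criterion, since failure to complete cannot be known before randomisation.

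3. The conflict with Treatment and intervention is limited. That section covers surgery considered at the end of week 8 or carried out in follow-up, and so does not reach surgery before week 8. What it promises is recording of medication and treatment, not continued outcome scans.

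4. A reader might conclude that the safety results would no longer rest on the randomised patients. That goes too far. The SAE itself is reported within 24 hours and entered in the CRF with severity, relationship and treatment, and confirmed side effects are followed. Only what happens afterwards to the remaining removed patients is in doubt.

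On size, power stays above the planned 80% at f = 0.3 and 0.5. The serious loss at f = 0.8 needs 40 of 100 placebo patients and 28% of all patients (56 of 200) removed, more than the plan's 20% drop-out. That is fair, and it is why the figures are offered as scenarios only.

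**Conclusion.** The point holds in this form. Three explicit rules order post-randomisation removal without separating study drug from trial participation, and they disagree with Concomitant care, Table 2, Treatment and intervention and a later sentence of Methodology. Followed as written, they make some week-8 volumes missing for reasons related to outcome or treatment, so the primary comparison is exposed to bias and later safety follow-up may be cut short.

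The direction and size cannot be fixed from the document. The scenario figures rest on assumed removal shares, on the plan's responder rates standing in for a continuous volume change, and on an analysis of retained patients only. Within those assumptions the consequence ranges from a modest dilution (30 to 26.3 points) to a large one (11.9 points), or to a type I error of about 0.15 when removal is unequal and there is no effect. The defect is in data collection, so it has to be corrected in the protocol.

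**What to change.** - Reconcile Methodology, SAEs, Concomitant care, Treatment and intervention, and Table 2 so that each kind of patient is handled in one stated way.
- Replace the removal and exclusion wording with a statement that, whatever is decided clinically about study drug or surgery, the patient stays in all scheduled CT, functional and safety assessments to week 24 and is analysed in the randomised arm.
- State in advance how patients operated on before week 8 enter the primary analysis. The emergency CT that the plan already obtains is one option, with a sensitivity analysis counting surgery as failure. It would not cover patients removed for an SAE or a side effect, for whom continued scheduled scans are the remedy.
- Reword exclusion item 10 as a judgement made before randomisation.

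The cost is an amendment and retained visits for a minority of patients; no extra patients are needed. With 96 of 200 enrolled at the time of the article, the change could still cover the other 104 in full, as well as any enrolled patients still under observation.

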### Timeline schedule

Protocol-mandated assessments will be performed according to the schedule (Table 2). The study flow chart illustrates key steps of the trial (Fig. 1).

**Table 2 Tab2:** Visit and assessment schedule

Activities	Screening	Day 1	Days 2–6	Day 7	Week 2 ± 1D	Week 3 ± 1D	Week 4 ± 1D	Week 8 ± 3D (treatment end)	Week 12 ± 3D^4^	Week 24 ± 7D^4^
Informed consent	√									
History collection										
Inclusion/Exclusion	√									
Concomitant medication^1^		√	√	√	√	√	√	√	√	√
Physical examination	√			√	√	√	√	√	√	√
Surgery conversion		√	√	√	√	√	√	√	√	√
Efficiency observation										
Neurological symptoms^2^	√	√	√	√	√	√	√	√	√	√
Hematoma volume by CT^2^	√						√	√	√	√
MGS-GCS/ADL-BI^2^	√			√			√	√	√	√
GOS							√	√	√	√
Safety assessment										
Vital signs	√	√	√	√	√	√	√	√	√	√
Blood routine/Coagulation	√						√	√	√	√
Liver and renal function/Electrolyte/Lipids	√						√	√	√	√
Urinalysis	√							√		√
Electrocardiography	√							√		√
Pregnancy test	√									
Adverse events		√	√	√	√	√	√	√	√	√
Others										
Drug dispensing	√			√	√	√	√			
Drug recovery^3^				√	√	√	√	√		

*ADL-BI* Activities of Daily Life – the Barthel Index scale, *CT* computerized tomography, *D* day, *GOS* Glasgow Outcome Score, *MGS-GCS* Markwalder’s Grading Scale and Glasgow Coma Scale

^1^Records of combination therapy are required until the end of the trial

^2^Surgical therapy is considered in the case of deterioration in neurological symptoms and/or signs, MGS-GCS grading and increase of hematoma immediately imaging review then

^3^The remaining drugs need to be recovered

^4^At weeks 12 and 24, CT should be performed; other laboratory examinations will be selected when needed

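### Removal after any SAE, and exclusion on suspicion of a side effect, can end follow-up and lose the week-8 CT unless the event is confirmed as atorvastatin-related

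*Protocol article*

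**What the plan says.** The Methodology section of the protocol article gives two successive rules for side effects. On suspicion: "If a patient develops any suspected related side effects, he or she will be immediately excluded". On confirmation: "If atorvastatin-related side effects are confirmed, treatment will be terminated and affected patients will be followed for 6 months".

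The SAEs section has its own rule: "Once a SAE is confirmed in a patient, this patient will be removed from the trial". Besides death, threat to life and lasting injury, its definition covers "hospitalization for emergencies or prolonged hospitalization". It then requires a report within 24 hours, a full report to the sponsor and the regulator, and case report form entries on severity, relationship and treatment. An ethics committee "will conduct an investigation to identify causes of SAEs". It mentions no further visits.

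The Concomitant care section says that patients whose deficits progress may be admitted, and then: "Whether these patients remain on the trial as inpatients will be determined on a case-by-case basis by two participating investigators/surgeons".

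The Outcomes section states: "The primary outcome is the change of hematoma volume 8 weeks after atorvastatin treatment on non-enhanced CT scan". The Abstract places this at the end of the 8-week treatment. In Table 2 (Timeline schedule) the row "Hematoma volume by CT" is ticked at screening and at weeks 4, 8, 12 and 24. Neither the table nor its footnotes say what happens to these visits once a patient has been excluded or removed.

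**The concern.** Stopping study drug and leaving the trial are different things, and these rules do not keep them apart. If they are followed literally, whether a patient is still observed after an event depends on a later judgment of cause. The patients who drop out of view are those whose event was serious but not attributed to atorvastatin and, on one reading, those whose side effect was suspected but never confirmed.

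Two things are at stake. The first is safety: scheduled adverse-event assessments stop for patients who have just had an event. The second is efficacy. Study drug is taken up to week 8 and the primary CT falls at week 8, so a patient who leaves for an event earlier in treatment has no primary outcome. After an emergency admission for neurological worsening, that missing hematoma volume is plausibly related to what it would have shown.

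**Working it through.** The plan states no figure on this point, so the check is a comparison of sections and a count from Table 2.

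**1. Which patients have follow-up stated**

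| Event | Stated action | Follow-up stated |
|---|---|---|
| Suspected side effect, never confirmed | Excluded (Methodology) | None |
| Side effect confirmed as atorvastatin-related | Treatment stopped (Methodology) | 6 months |
| SAE confirmed as atorvastatin-related | Removed (SAEs); also within the Methodology rule | Arguably 6 months |
| SAE not confirmed as related | Removed (SAEs) | None |
| Admission for progressing deficits | Case by case (Concomitant care); removed if it is an SAE | The two rules conflict |

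Removal after an SAE does not wait for a causality verdict. It follows once the SAE is confirmed, and the cause is investigated separately.

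**2. What the terms mean.** *Excluded* is undefined and could mean off drug only. *Removed from the trial* is harder to read that way, because Concomitant care uses remaining on the trial for continued participation. The SAEs section is therefore the firmer basis.

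**3. Whether another section restores the visits.** Treatment and intervention promises recording to 24 weeks, but of medication and treatment, and for patients whose hematoma does not shrink, grows, or whose deficits progress. It is not a rule for side effects or SAEs, and it promises neither safety visits nor the week-8 CT. Methodology provides an emergency CT at neurological deterioration. That is not the week-8 measurement.

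**4. Visits lost per patient.** Ticks in Table 2:
- Adverse events: day 1, days 2–6, day 7, weeks 2, 3, 4, 8, 12, 24.
- CT: screening, weeks 4, 8, 12, 24.
- MGS-GCS/ADL-BI: screening, day 7, weeks 4, 8, 12, 24.

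| Leaves after | Adverse-event assessments lost | CTs lost | MGS-GCS/ADL-BI lost | Primary CT lost? |
|---|---|---|---|---|
| Day 7 | 6 (weeks 2, 3, 4, 8, 12, 24) | 4 (weeks 4, 8, 12, 24) | 4 (same weeks as CT) | Yes |
| Week 4 | 3 (weeks 8, 12, 24) | 3 | 3 | Yes |
| Week 8 | 2 (weeks 12, 24) | 2 | 2 | No |

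**5. Power.** The Sample size section assumes 80 % against 50 % responders and asks for 52 per arm. With n = [1.960·√(2·0.65·0.35) + z·√(0.16 + 0.25)]² / 0.30², two-sided 0.05, n is 39 at 80 % power and 52 at 90 %. The stated 52 thus fits 90 % rather than the stated 80 %, which is a separate matter. The plan recruits 100 per arm. Under the same assumptions power is 99.6 % with no losses, 98.3 % with 20 % lost (80 per arm) and 94.1 % with 40 % lost (60 per arm).

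**6. Direction of any bias, on assumed rates.** Suppose the true response is 50 % in both arms and every removed patient is a non-responder. The observed rate in an arm is then 0.50/(1 − share removed).
- 5 % removed in each arm: 0.526 − 0.526 = 0.
- 10 % atorvastatin, 5 % placebo: 0.556 − 0.526 = +2.9 points (0.0292 before rounding).
- 20 % atorvastatin, 5 % placebo: 0.625 − 0.526 = +9.9 points.
- With the shares reversed, the sign reverses.

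These shares are illustrations; the article gives none.

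**The case against.** The strongest reply is that this is loose wording in a condensed article. *Excluded* may mean only that study drug stops. Methodology speaks of terminating treatment at the later, confirmed step, which can be argued either way: the authors have a separate term for stopping drug, or the patient is still under evaluation after being excluded. Withdrawal procedures and following events to resolution are commonly left to the full protocol, which is not shown. The SAEs section also requires reporting and an inquiry into cause, so attention does not end at the event. This stands for *excluded*, and that branch is therefore conditional. It does not answer the SAEs section, which states outright that the patient leaves the trial, nor the conflict with Concomitant care.

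A reader might infer that every SAE ends observation. That goes too far: nothing in the Methodology rule exempts serious events, so an SAE confirmed as atorvastatin-related arguably gets the 6 months. For the same reason, it would be wrong to say that the trial cannot see whether myopathy resolves off drug, as the Discussion expects; confirmed cases are followed.

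A reader might also infer that all the missing values track the patient's hematoma. The documents give no link between hematoma volume and a suspected statin side effect such as a muscle complaint or a liver-test change. The link is plausible only for events such as neurological SAEs.

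**Conclusion.** The point holds in limited form. As written, a patient with an SAE not confirmed as atorvastatin-related leaves the trial with no visits stated afterwards. A patient with a suspected but unconfirmed side effect does too, if *excluded* means leaving. Departure after day 7 costs 6 adverse-event assessments, 4 CTs and 4 clinical-scale assessments; after week 4, 3 of each; after week 8, 2 of each. The primary CT is lost in the first two cases. Separately, an admission for neurological worsening can fall under two incompatible rules, so two sites could handle the same patient differently and both be following the article.

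This rests on the literal wording and on the absence of an overriding rule in the full protocol. A reader might go on to infer a biased treatment comparison or an underpowered trial. Neither is shown: the rules apply to both arms, no rate of suspected effects or SAEs is given, the illustrated bias is zero when removals are equal and can take either sign, and 100 per arm leaves ample room under the plan's own assumptions. The matter deserves correction but does not by itself invalidate the trial.

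**What to change.** Amend the SAEs and Methodology sections so that a suspected related side effect or an SAE stops study drug when clinically indicated but leaves the patient in the trial. Continue the Table 2 visits (adverse events, CT including week 8, MGS-GCS/ADL-BI) to week 24 in both arms, whatever the causality verdict, unless consent is withdrawn. State that *excluded* and *removed* mean off study drug, and align the case-by-case wording in Concomitant care with this.

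The change adds no new type of visit. Its cost is a mid-trial amendment that may need approval at the 16 participating centers, plus attendance at scheduled visits by patients who would otherwise have left. With 96 of 200 enrolled, it can cover the remaining 200 − 96 = 104 and those already enrolled who are still within their 24 weeks. It cannot recover data from patients already removed.
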